## Abstract

**Background:**

Idiopathic pulmonary fibrosis (IPF) is characterized by a poor prognosis, with a progressive decline in lung function and considerable variability in the disease’s natural history. Besides lung transplantation (LTx), the only available treatments are anti-fibrosing drugs, which have shown to slow down the disease course. Therefore, predicting the prognosis is of pivotal importance to avoid treatment delays, which may be fatal for patients with a high risk of progression. Previous studies showed that a multi-dimensional approach is practical and effective in the development of a reliable prognostic score for IPF. In the RIsk Stratification scorE (RISE), physiological parameters, an objective measure of patient-reported dyspnea and exercise capacity are combined to capture different domains of the complex pathophysiology of IPF.

**Methods:**

This is an observational, multi-centre, prospective cohort study, designed to reflect common clinical practice in IPF. A development cohort and a validation cohort will be included. Patients newly diagnosed with IPF based on the ATS/ERS criteria and multi-disciplinary discussion will be included in the study. A panel of chest radiologists and lung pathologists will further assess eligibility. At the first visit (time of diagnosis), and every 4-months, MRC dyspnea score, pulmonary function tests (FEV_1_, FVC and DLCO), and 6-min walking distance will be recorded. Patients will be prospectively followed for 3 years. Comorbidities will be considered. The radiographic extent of fibrosis on HRCT will be recalculated at a 2-year interval. RISE, Gender-Age-Physiology, CPI and Mortality Risk Scoring System will be calculated at 4-month intervals. Longitudinal changes of each variable considered will be assessed. The primary endpoint is 3-year LTx-free survival from the time of diagnosis. Secondary endpoints include several, clinically-relevant information to ensure reproducibility of results across a wide range of disease severity and in concomitance of associated pulmonary hypertension or emphysema.

**Discussion:**

The objective of this study is to validate RISE as a simple, straightforward, inexpensive and reproducible tool to guide clinical decision making in IPF, and potentially as an endpoint for future clinical trials.

*Trial registration*: U.S National Library of Medicine Clinicaltrials.gov, trial n. NCT02632123 “Validation of the risk stratification score in idiopathic pulmonary fibrosis”. Date of registration: December 16th, 2015.

## Background

Idiopathic pulmonary fibrosis (IPF) is a chronic, progressive lung disease characterized by lung scarring and by the histologic pattern of usual interstitial pneumonia (UIP) [1]. IPF has a mean survival time of only 3 to 5 years from the time of diagnosis, in the absence of therapy [2–4]. Currently the estimated incidence of IPF is in the range of 2–30 cases per 100,000 person-years, while estimated prevalence is 10 to 60 cases per 100,000 people [1]. As the global incidence of IPF and associated rates of morbidity, mortality and economic burden of healthcare utilization continue to rise [5], improved prognostic tools are needed. Clinical outcomes of IPF are highly variable and difficult to predict, and disease progression may not proceed in a linear fashion. There is the need for a validated staging system to guide clinicians in providing individualized care for patients with IPF, particularly when choosing the optimal type and timing of therapeutic options, including lung transplantation (LTx) referral, assessment and listing.

After diagnosis, the major challenge with management of IPF is represented by the difficulty in determining the clinical course of the disease and promptly detecting clinically significant progression. Uncertainty around clinical progression could impact the timing of initiating anti-fibrotic treatment to slow the progression of fibrosis, or could delay the timing of LTx assessment. Furthermore, the rate of progression of IPF is highly variable both between and within individual patients [6]. The rate of deterioration and progression in IPF is variable, with some patients experiencing a stepwise rather than steady decline [4], even after prolonged periods of stability. Progression of disease in IPF can be further complicated by the occurrence of acute exacerbation (AEs), defined as a sudden acceleration of the disease, with a rate of mortality upwards of 50% [7]. Symptom progression may advance or change quickly even for an individual patient, further necessitating a reliable staging tool that can be used to  make a valid prognostic evaluation and guide changes to the treatment plan.

Multi-dimensional scores are more likely to capture the complex pathophysiology of IPF, where gas exchange and ventilatory impairments, excessive dead space ventilation, increased elastic inspiratory load, muscle dysfunction and associated pulmonary hypertension (APH) may establish a complex and variable interplay [10].

We previously demonstrated that exertional dyspnea measured with the Medical Research Council dyspnea score (MRCDS), lung function and 6-min walk distance (6MWD) are significant and independent predictors of survival in IPF, with no observed collinearity among them [8]. The independence of the 3 domains (dyspnea, lung function, exercise capacity) was demonstrated in a prospective study [3] and in a multi-centre study as well [9].

The Risk Stratification Score (RISE) was first developed in a cohort of patients with IPF who were prospectively followed, and tested in another, retrospectively enrolled cohort. The acronym was later changed from ROSE to avoid confusion with “rapid onsite evaluation”. Capturing each of the 3 aforementioned domains, RISE is based on MRCDS, Composite Physiologic Index (CPI) and 6MWD. RISE was demonstrated to be superior to individual variables in predicting LTx-free survival [3]. We subsequently demonstrated that RISE was a reliable predictor of mortality in patients assessed for LTx [9], and also able to capture patient response to anti-fibrotic therapy better than the commonly used variables [11]. However, the main limitations of the 2012 study were the size of the prospective cohort, and the lack of prospective validation.

The current approach to the detection of progression of disease in IPF is largely based on forced vital capacity (FVC) changes and high-resolution chest CT scan (HRCT). We recently demonstrated that the prognostic accuracy of a decline of FVC combined with an increase of the extent fibrosis on HRCT (visual score) is far from being optimal, although the 2 variables are independent from each other [12]. This finding further strengthens the rationale for pursuing the development and validation of an integrated, multi-dimensional prognostic tool for IPF. As a more recent development, we tested a modified version of CPI against the original one, and found the new CALIPER-based CPI to be a stronger predictor of survival in IPF [13], making it a candidate component of the RISE.

The main objective of the study is to test and validate a modified version of the RISE in 2 separate cohorts of patients with IPF, prospectively followed from the time of diagnosis. To our knowledge, no previous, large scale, prospective, 3-year observational study has been conducted to validate a multi-dimensional staging system for IPF.

We hypothesize that both RISE at baseline and its longitudinal changes are the best predictors of survival in patients newly diagnosed with IPF followed for a period of 3 years, both in terms of sensitivity and specificity. The prognostic power of RISE will be compared to the current standard of care (individual pulmonary function tests, 6MWD, HRCT chest scan fibrosis score) and with other multi-dimensional scores as well, namely Gender-Age-Physiology (GAP) Index [14], CPI (both original and CALIPER-revised versions) [15, 16] and Mortality Risk Scoring System (MRSS) [17].

## Methods and design

This is an observational, international, prospective cohort study including 2 large tertiary referral centres for interstitial lung disease (ILD) (London, Canada and Rome, Italy). The study was designed to reflect common clinical practice in IPF.

Only patients newly diagnosed with IPF based on the American Thoracic Society/European Respiratory Society (ATS/ERS) criteria [1] and local multi-disciplinary discussion (MDD) [18] at participating centres will be included in the study. As a further inclusion step, for all patients who did not undergo a surgical lung biopsy (SLB), a panel of 3 chest radiologists with ILD expertise will examine each HRCT, and patients will be included, if at least 2 out of 3 agree on a pattern of probable/definite UIP. For patients who underwent a SLB, a panel of 3 lung pathologists with ILD expertise will examine each biopsy, and patients will be included if at least 2 out of 3 agree on a pattern of probable/definite UIP.

All known causes of ILD will carefully excluded before each patient is included in the study. These include domestic, environmental, occupational, exposures; drug-induced lung toxicity; and connective tissue diseases. Comorbidities considered will include APH (only if right heart catheterization[RHC]-proven), chronic obstructive pulmonary disease (COPD), coronary artery disease (CAD), left heart dysfunction (LHD), and sleep apnea (SA).

A development cohort and a validation cohort will be included in the study. In both cohorts, at the first visit (time of diagnosis) and at each subsequent visit at 4-month intervals, for a period of 3 years, MRCDS (Table 1), pulmonary function tests (PFTs)(forced expiratory volume during the first second [FEV_1_], FVC, diffusing lung capacity for carbon monoxide [DLCO]), and 6MWD will be obtained. 6MWD % predicted will be calculated, as previously described [19]. The use of supplemental oxygen and the level of oxygen desaturation will be considered. The following events will be recorded in the study: death; LTx referral; LTx; AEs; hospitalization for respiratory causes; start, stop and switch of anti-fibrotic therapy; start of supplemental home oxygen therapy; start and stop of physiotherapy program enrolments; progression of disease (see Secondary endpoints).

**Table 1 Tab1:** MRC dyspnea score (0 to 5 scale) [20]

Grade	Description
0	I only get breathless with strenuous exercise
1	I get short of breath when hurrying on level ground or walking up a slight hill
2	On level ground, I walk slower than people of the same age because of breathlessness
3	On level ground, I have to stop for breath when walking at my own pace
4	I stop for breath after walking about 100 m or after 5 min on level ground
5	I am too breathless to leave the house or I am breathless when dressing

The RISE (Table 2) will be first calculated, as previously described, on a scale from 1 to 3 [3]. However, a modified and improved version of the RISE will also be considered, using the CALIPER-revised CPI instead of the original version of CPI [13], and with a new 1 to 4 scale, which may allow for better stratification for mortality risk (Table 2). If superior to the previous version of RISE, the modified version will be tested for validation.

**Table 2 Tab2:** Risk Stratification Score (RISE) (revised)

RISE components: 1. MRCDS ≥ selected cutoff* 2. 6MWD % pred ≤ selected cutoff* 3. CPI ≥ selected cutoff*	RISE
No parameter met	0
One parameter met	1
Two parameters met	2
Three parameters met	3

MRCDS: MRC dyspnea score; 6MWD: 6-min walk distance; CPI: Composite Physiologic Index (CALIPER-revised version)

^*^selected cut-offs for each variable will be determined by receiver operating characteristics analysis (c-statistics)

Patients will be prospectively followed for a period of 3 years from the time of diagnosis and enrolment. All multi-dimensional scores will be calculated at 4-months intervals corresponding to each visit. A 2nd HRCT will be obtained at the 2-year visit, or sooner if clinically indicated, and as per clinicians’ discretion. The HRCT fibrosis score [12] will be then recalculated on the 2nd scan. Deaths, LTx, AEs and hospitalizations due to respiratory causes will be recorded. All protocol violations (missed visits, delayed visits, data not obtained at individual visits) will be systematically recorded. Every interruption or change in course of therapy will be recorded. When available, hemodynamic data from RHCs will be considered. Since 2D echocardiograms alone are unreliable in predicting the presence of APH in IPF [21], they will not be considered.

At the end of the study period, both baseline RISE and longitudinal changes of RISE will be tested as predictors of mortality. Other individual variables will also be tested as predictors of mortality, including age at the time of diagnosis, time between onset of symptoms and diagnosis (months), gender, body mass index, smoking history (pack-years), FVC, DLCO, 6MWD (meters and % predicted), desaturation during 6-min walk test, HRCT visual fibrosis score at the time of diagnosis, and other multi-dimensional scores (GAP, CPI, MRSS). In the validation cohort, we will seek to confirm and validate results obtained in the development cohort.

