### Secondary endpoints

Comparative analysis of RISE as predictor of LTx-free survival in subgroups stratified by age; gender; baseline lung function; baseline 6MWD; baseline extent of fibrosis on HRCT; time between onset of symptoms and diagnosis; presence of APH; presence of concomitant emphysema; presence of comorbidities (COPD, CAD, LHD, SA); participating site.Clinical progression, as a predictor of mortality, defined as either: absolute decline of FVC >10% pred; decline of 6-min walk distance >50 m; hospitalization for respiratory causes; LTx assessment; or death.Incidence of AEs of IPF and its predictors, if any.Incidence of hospitalizations due to respiratory causes and its predictors, if any.LTx-free survival, incidence of AEs, incidence of hospitalizations, and time to progression of patients with HRCT pattern definite/probable for UIP vs. patients with indeterminate/inconsistent pattern. In this subanalysis, 2 groups of patients matched for age, gender, BMI, and extent of fibrosis at the time of diagnosis will be considered.LTx-free survival, incidence of AEs, incidence of hospitalizations, and time to progression of patients with autoimmune markers (although not meeting criteria for interstitial pneumonia with autoimmune features [23] versus those without. In this subanalysis, 2 groups of patients matched for age, gender, BMI and extent of fibrosis at the time of diagnosis will be considered.LTx-free survival, incidence of AEs, incidence of hospitalizations and time to progression of patients with concomitant emphysema versus those without. In this subanalysis, 2 groups of patients matched for age, gender, BMI and extent of fibrosis at the time of diagnosis will be considered.LTx-free survival, incidence of AEs, incidence of hospitalizations and time to progression of patients treated with pirfenidone versus patients treated with nintedanib. In this subanalysis, 2 groups of patients matched for age, gender, BMI and extent of fibrosis at the time of diagnosis will be considered.LTx-free survival, incidence of AEs, incidence of hospitalizations and time to progression of patients whose therapy was switched (from pirfenidone to nintedanib and viceversa). In this subanalysis, 2 groups of patients matched for age, gender, BMI and extent of fibrosis at the time of diagnosis will be considered.6MWD m versus % pred as predictors of mortality.Survival, incidence of AEs and time to progression on the LTx waitlist of listed patients.Time to progression in patients with initially non-clinically significant disease.Long-term follow-up (beyond 3 years) of patients who are still alive without a LTx, until required recruitment is completed. This will include LTx-free survival, incidence of AEs, incidence of hospitalizations and time to progression.

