### Longitudinal follow-up

After diagnosis, patients are seen at 4-month intervals, for a period of 3 years in both the development and validation cohort. At each visit, MRCDS, PFTs and 6MWT will be obtained. Patients may be seen at closer intervals between visits, at the clinician’s discretion. After completion of the 3 years follow-up period, patients who are still alive without a LTx will continue to be followed regularly until required recruitment is completed, as long-term follow-up is part of secondary endpoints.

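### APH counts only if catheter-proven, so never-catheterised patients would fall in with the catheter-negative ones and make the APH subgroup result hard to trust

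*Protocol article*

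**What the plan says.** All references are to the protocol article.

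- **Definition.** Methods and design lists the comorbidities: "Comorbidities considered will include APH (only if right heart catheterization[RHC]-proven").
- **Source of the data.** The same section says: "When available, hemodynamic data from RHCs will be considered". No sentence requires RHC for every patient.
- **No substitute test.** "Since 2D echocardiograms alone are unreliable in predicting the presence of APH in IPF [21], they will not be considered".
- **Scheduled assessments.** Longitudinal follow-up says: "At each visit, MRCDS, PFTs and 6MWT will be obtained". RHC is not in that list.
- **Setting.** "The study was designed to reflect common clinical practice in IPF".
- **Use of APH.** The first item under Secondary endpoints is "Comparative analysis of RISE as predictor of LTx-free survival in subgroups stratified by age; gender; baseline lung function", and the list of stratifiers continues with "presence of APH; presence of concomitant emphysema". The abstract (Methods) says the secondary endpoints are to show that results are reproducible "in concomitance of associated pulmonary hypertension or emphysema".

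**The concern.** Each rule is reasonable alone. The difficulty comes from combining them. The definition is one-sided: it says what makes a patient APH-positive, and the only route is a positive RHC. A stratifier based on presence needs the other side as well. A patient without RHC cannot be present, and the natural place left is absent, next to patients in whom RHC ruled APH out. The plan sets echocardiography aside as unreliable for this purpose, yet the rule in effect lets the lack of any test stand as a negative test.

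Timing adds a second problem. The stratifier list ties lung function, 6MWD and extent of fibrosis to baseline, but gives no time point for APH. Patients are followed for 3 years in ordinary practice, so a first RHC could come well after diagnosis, plausibly at transplant assessment. Transplantation is part of the primary endpoint. APH status could then depend on later events linked to the outcome, and on surviving long enough to be tested.

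What is at stake is one claim: that RISE performs reliably with and without APH. Without a separate level for untested patients, a reader could not tell whether RISE works in patients without APH or only in patients who were mostly never tested for it.

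**Working it through.** **Figures in the plan.** The only relevant number is the sample size of 125 per cohort (Statistical analysis and sample size calculation). The inputs behind it are not given, so it is taken as stated; the point does not depend on how it was derived. The article gives no RHC rate and no APH prevalence, so the rest is illustration on assumed values.

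**Assumptions.**
- f = share of patients with RHC: 20% to 50%
- APH rate among tested patients: 40%
- u = APH rate among untested patients: 10% to 30%

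**Formulas, per cohort of 125, with untested patients counted as absent.**
- Proven = 125 × f × 0.4
- Excluded = 125 × f × 0.6
- Not done = 125 × (1 − f)
- Hidden APH = 125 × (1 − f) × u
- Absent stratum = excluded + not done
- Hidden share = hidden APH / absent stratum

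| f | u | Proven | Excluded | Not done | Hidden APH | Absent stratum | Hidden share |
|---|---|---|---|---|---|---|---|
| 50% | 10% | 25 | 37.5 | 62.5 | 6.25 | 100 | 6.25% |
| 50% | 30% | 25 | 37.5 | 62.5 | 18.75 | 100 | 18.75% |
| 20% | 10% | 10 | 15 | 100 | 10 | 115 | 8.7% |
| 20% | 30% | 10 | 15 | 100 | 30 | 115 | 26.1% |

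Undetected APH therefore makes up about 6% to 26% of the absent stratum. Untested patients make up 62.5/100 = 62.5% to 100/115 = 87% of it. The share of all APH that goes undetected is larger, 6.25/31.25 = 20% to 30/40 = 75%. The 6% to 26% figure is the one that bears on the purity of the absent stratum.

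**A second parametrisation.** Let p be the true APH prevalence and t the share of APH patients who have an RHC. The hidden share is p(1 − t)/(1 − pt).
- p = 30%, t = 30%: 0.21/0.91 = 23%.
- p = 10%, t = 60%: 0.04/0.94 = 4%.
- p = 50%, t = 10%: 0.45/0.95 = 47%.
- t = 100%: 0.

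The result is driven by how completely APH patients are catheterised, which the article does not give.

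**What this does not compute.** These are shares of misplaced patients. They do not measure any change in how well RISE discriminates within a stratum; that depends on who is catheterised and how RISE behaves in those patients, and the article gives no figure for either.

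**The case against.** **The article never assigns untested patients to the absent group.** This is correct. A fuller document could use an unknown category or restrict the analysis to catheterised patients, and a journal article commonly leaves coding to such a document. A reader might infer that the protocol expressly files untested patients as free of APH; no sentence says so. What stands is that the article does more than stay silent. It states a rule under which untested patients can never be positive and then uses presence as a stratifier. Restricting to catheterised patients would also need stating, because it replaces misplacement with selection.

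**Bias is not shown.** A reader might infer that the subgroup result is certainly biased, or wrong in both strata. The documents do not support that. The endpoint is the performance of RISE within strata, not the effect of APH itself. The APH-present stratum holds only proven cases; it may be selected, but the rule does not contaminate it. That RHC goes mainly to sicker or transplant-assessed patients is an inference, since no indication for RHC is given.

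**The definition is defensible.** This stands in full. Requiring RHC proof is specific, and the reason for setting echocardiography aside is given. Nor does the article say that catheterisation is performed only when available; it says the data are considered when available. The weakness lies in the status of patients without RHC, not in the standard of proof.

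**Conclusion.** The point holds in a limited form. Read as written, the APH-absent stratum would pool RHC-negative with never-tested patients and contain an unknown share of undetected APH: about 6% to 26% under assumed RHC in 20% to 50%, APH in 40% of tested and 10% to 30% of untested patients. Because no time point is set for APH, status may also reflect post-baseline testing linked to transplant assessment. The APH subgroup result is likely to be unreliable; neither the direction nor the size of any bias in RISE performance can be fixed from the article.

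The reach is narrow. This is one stratifier of one secondary endpoint. A reader might infer that the validation of RISE as a whole is affected, but APH enters neither the primary endpoint nor the RISE components, and nothing in the sample size description refers to it. The change is still worth making, because it costs little and the abstract names APH as a setting in which results should be reproducible.

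**What to change.** - Code APH in three levels: RHC-proven, RHC-excluded, RHC not done. Do not merge the third level with the second.
- Fix status from RHCs near diagnosis, within a window stated in advance, so that later testing does not define a stratum.
- Report the number, timing and indication of RHCs, and the performance of RISE in each of the three levels.
- Treat proven versus excluded among catheterised patients as exploratory. It is small, and it keeps whatever selection determined who was catheterised.

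**Cost.** One coding rule and some extra reporting; no added procedure. The price is smaller strata and wider intervals. If RHC is done in 20% of patients, a cohort of 125 yields 25 catheterised patients, 10 proven and 15 excluded on the assumed 40% rate; at 50% it yields about 62, roughly 25 and 37. The restriction to RHCs near diagnosis would reduce these further, and results in catheterised patients may not generalise to the rest.

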### Statistical analysis and sample size calculation

The distribution of variables considered will be analysed with Kolmogorov–Smirnov test. Interobserver variability among chest radiologists and lung pathologists will be assessed with Weighted kappa coefficients [29]. Survivors and non-survivors will be compared by using the unpaired t-test, or, for not normally distribute variables, with the Mann–Whitney U-test. To rule out multicollinearity and demonstrate that included variables are truly independent, variance inflation factors of the RISE components will be calculated [30]. Receiver operating characteristics analysis will be used to identify the most accurate cut-off values for each variable to predict endpoints. Multivariate analysis of significant predictors of endpoints will be conducted with the Cox proportional hazard model. Results will be summarized as hazard ratios. Once patients are listed for LTx, death and LTx become competing events. To account for the competing risks of LTx and death in the population of patients undergoing LTx assessment, the Fine-Gray competing risk regression model [31] will be used. This will identify variables significantly predicting independent survival status and results will be summarized as subdistribution hazard ratios. These represent the relative risk of dying prior to LTx. Survival will be further evaluated using Kaplan–Meier curves and the log-rank test. Sample size calculation for an observational, cohort study was conducted using the methodology described by Wang and Ji [32], with the assistance of a statistician. Using available, preliminary data on 109 patients, dropout rate, ratio of low RISE to high RISE, and mortality rates in low RISE and high RISE subgroups were determined. With a power (probability of detecting a real effect) of 90%, and with a conservative approach, a sample size of 125 patients for each cohort was determined to be required.

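### The rule that promotes the modified RISE appears to compare ROC-tuned cut-offs with an untuned original in the same patients, which overstates the modified score's advantage

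*Protocol article*

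**What the plan says.** All references are to the protocol article.

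- **Original score.** Methods and design says that the RISE "will be first calculated, as previously described, on a scale from 1 to 3 [3".
- **Modified score.** The same paragraph adds a version that uses the CALIPER-revised CPI, "with a new 1 to 4 scale, which may allow for better stratification for mortality risk". The Table 2 footnote says that "selected cut-offs for each variable will be determined by receiver operating characteristics analysis (c-statistics".
- **Target of the tuning.** Statistical analysis and sample size calculation says: "Receiver operating characteristics analysis will be used to identify the most accurate cut-off values for each variable to predict endpoints". The endpoints are in the plural.
- **Promotion rule.** "If superior to the previous version of RISE, the modified version will be tested for validation". No measure, margin, test or optimism correction is attached to it.
- **Order of the cohorts.** "In the validation cohort, we will seek to confirm and validate results obtained in the development cohort". Each cohort is to have 125 patients.
- **Scale.** The text gives the revised score "with a new 1 to 4 scale", but Table 2 scores it 0 to 3.

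**The concern.** A score whose cut-offs were chosen to separate outcomes in a set of patients will look better in those patients than in new ones. A score with cut-offs fixed beforehand gets no such lift. If the two are compared in the tuning data, the difference contains the tuning gain as well as any real improvement, and the rule acts on the sum.

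Validating a modified RISE is the study's main objective, so this rule decides which score the second cohort is used for. At stake are two things: replacing the published score with one that is no better, and reporting tuning gain as progress over it.

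**Working it through.** **The plan's own figure.** The article gives no figure for the promotion rule. The only related figure is 125 per cohort. No event rate, AUC or original cut-off is given, so everything below except n is an assumption.

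**Set-up.** There are three components with pairwise correlation ρ. Death by 3 years is binary and follows a logistic model with the same coefficient β for each component. MRC dyspnea has six grades; walk distance and CPI are in whole numbers. The two CPI versions are equally prognostic. The original uses the cut-offs that are optimal in a population of 200,000. The modified score uses the cut-offs that maximise sensitivity + specificity − 1 in the same 125 patients. Each row below has 600 runs, so the Monte Carlo standard error of a proportion near 0.967 is √(0.967 × 0.033 / 600) = 0.007. Gains are mean differences in apparent AUC.

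| ρ, β, event rate | True AUC, original: 4-level / 3-level | Gain over 4-level | Modified higher | Paired test z > 1.96 | Gain over 3-level | Modified higher | Paired test z > 1.96 |
|---|---|---|---|---|---|---|---|
| 0.3, 0.5, 38% | 0.713 / 0.675 | 0.045 | 96.7% | 30.7% | 0.082 | 99.8% | 72.3% |
| 0.5, 0.4, 38% | 0.704 / 0.683 | 0.042 | 97.3% | 28.7% | 0.065 | 99.2% | 57.5% |
| 0.3, 0.8, 40% | 0.786 / 0.731 | 0.034 | 95.2% | 20.5% | 0.089 | 100% | 86.7% |
| 0.3, 0.5, 27% | 0.715 / 0.678 | 0.049 | 97.5% | 29.3% | 0.085 | 100% | 69.7% |

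**Step 1: tuning alone.** Against the four-level original the true difference is zero by construction, so the gain of 0.034-0.049 is an artefact. In new patients the tuned score is about 0.005-0.007 worse. Over all settings tried (events 27-50%), a paired test at z > 1.96 promotes it in about 20-40% of runs, against a nominal 2.5%.

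**Step 2: the three-level original.** The gain is tuning plus the real benefit of a fourth level. In row 1 the fourth level is worth 0.713 − 0.675 = 0.038, and 0.045 + 0.038 = 0.083, which agrees with the 0.082 observed. With a tuning loss of about 0.006 in new patients, the real gain and the overstatement are:

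- Row 1: 0.038 − 0.006 = 0.032; 0.082 / 0.032 = 2.6-fold.
- Row 2: 0.021 − 0.006 = 0.015; 0.065 / 0.015 = 4.3-fold.
- Row 3: 0.055 − 0.006 = 0.049; 0.089 / 0.049 = 1.8-fold.
- Row 4: 0.037 − 0.006 = 0.031; 0.085 / 0.031 = 2.7-fold.

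The real part is thus mostly 0.02-0.04, overstated roughly two- to four-fold.

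**Step 3: a revised CPI that is a worse marker.** With a true four-level difference of −0.012, the modified score still has the higher AUC in 88% of runs against the four-level original (13% by paired test).

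**Step 4: removing the asymmetry.** If both versions are re-tuned on one four-level scale, the mean difference is −0.001 to 0.001. The modified score is then higher in 47-53% of runs and significantly so in about 1%. If the original stays fixed and the modified AUC is bootstrap-corrected with the cut-off search repeated, the mean difference from the four-level original falls to 0.004-0.008 and the modified score is higher in 54-59%.

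**Step 5: the scale.** Table 2 has four levels, for none to three parameters met. On 0 to 3, a score of 2 means two parameters met; on 1 to 4 with the same ordering, it means one. This needs no assumption.

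**The case against.** **The premises are inferred.** No sentence says that the original's cut-offs stay fixed, or that tuning and comparison use the same patients. The RISE is introduced with a reference to Table 2, whose footnote prescribes ROC cut-offs, so both versions might be re-tuned; on one scale the bias would then largely vanish. This stands as a condition. But Table 2 is labelled as the revised score and defines its CPI as the CALIPER version, and the comparison comes before validation. The reading used here is therefore the plainest one.

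**Promotion may be the right decision.** Against a three-level original the modified score is usually truly better. If the published cut-offs do not suit this population, it can also beat a four-level original: in two settings with displaced cut-offs the true gains were 0.012 and 0.027. This stands. The apparent gains there were 0.069 and 0.081, so the excess was still 0.069 − 0.012 = 0.057 and 0.081 − 0.027 = 0.054.

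**The measure of superiority belongs in an analysis plan.** Its absence from an article is no fault. The point is that the rule as stated sets a tuned score against an untuned one.

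**Stronger readings the article does not support.**

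- *Promotion is automatic.* This nearly holds if superior means any higher AUC, which the article does not say. With a paired test, false promotion is inflated but not certain.
- *GAP, CPI and MRSS are untuned comparators.* The ROC sentence covers every variable, and these scores are among the predictors to be tested, so they may be tuned too.
- *Transplant recipients count as survivors in the ROC analysis.* The sentence "Survivors and non-survivors will be compared by using the unpaired t-test" concerns a group comparison, not the ROC, and no such coding is stated.
- *Validation can never reveal the error.* MRC dyspnea, lung function and walk distance are collected in both cohorts, so the original score can be calculated there. The article just does not commit to that comparison.

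**Conclusion.** The concern holds in a limited form. If the original's cut-offs are fixed and the comparison is made in the development patients, the promotion rule is biased towards the modified score by about 0.03-0.05 AUC at n = 125. With no true advantage over a four-level original, the modified score leads in about 95-100% of samples. Against the three-level original, the direction is usually right but the size is overstated.

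The figures rest on assumed event rates of 27-50%, correlations of 0.3-0.5, four-level AUCs of about 0.70-0.79, a binary 3-year outcome, and four counts collapsed to three levels for the original. They show the order of magnitude and do not predict this study's result.

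With locked cut-offs, the validation cohort still estimates the promoted score's own performance without bias. The damage is confined to the choice of version and to claims of improvement over the original RISE. The conflict between the two scales is certain, but it is a labelling matter and adds nothing to the bias.

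**What to change.** 1. Derive one set of cut-offs, in the development cohort only, for the primary endpoint.
2. Compare the two versions there with a bootstrap optimism-corrected C-index that repeats the cut-off search in each resample, and say what result counts as superior.
3. Lock the cut-offs and do not rerun the ROC analysis in the validation cohort.
4. Calculate both the original and the modified RISE in the validation cohort, and base any claim of superiority over the original on that cohort.
5. Use one scale for the revised score in the text and in Table 2.

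The cost is a change of wording and a little more analysis, with no new patients, visits or measurements. The modified score's advantage in the development cohort will look smaller. The changes should be made before outcomes are analysed.
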